### Experimental Design

This is a randomized, double-blind, placebo-controlled clinical trial of rTMS for the treatment of cognitive impairment in patients stratified by severity of Alzheimer dementia. Participants with probable Alzheimer disease will be recruited from the three sites contributing to the study (Winnipeg, Montreal, and Melbourne), and will be randomly assigned to either a 2-week, 4-week, or sham high-frequency rTMS treatment. Standard cognitive assessments will be performed before and after treatment, as well as at scheduled follow-up visits up to 6 months after the end of the intervention. Participants will be blind to the type of treatment (active vs placebo). Assessors will be blind to both the type and duration (2 vs 4 weeks) of treatment.

## Methods

### Recruitment

Recruitment for this study will be performed at all three sites. Patients with probable Alzheimer disease at mild to moderate stages will be recruited. The target recruitment rate of patients at each site is estimated to be approximately 25 per year, with a target total recruitment of 300 participants across all sites.

All potential participants must have been diagnosed with mild or moderate stage Alzheimer disease by their referring physician or one of our study doctors. The screening doctor will complete an eligibility assessment with the potential participants to confirm their suitability to participate in the study. This assessment will use the CDR [49] and MoCA [50] to assess the severity of dementia. In addition, they will complete the Cornell Scale for Depression in Dementia (CSDD) [51] to assess for comorbid depression. The screening doctor will also consider various inclusion and exclusion criteria.

The inclusion criteria are as follows (all must be met): age >55 years; MoCA score between 7 and 25; CDR score of 1 to 2; CSDD score of 18 or less to rule out moderate to severe depression; diagnosis of probable mild or moderate Alzheimer disease as confirmed by the treating neurologist, geriatrician, or psychiatrist, and/or by the study coinvestigators; and use of a stable dose or no dose of an acetylcholinesterase inhibitor for at least 3 months prior to study entry with no plans to change medication for the duration of the study. If a participant decides to discontinue an Alzheimer disease–related medication (ie, a cholinesterase inhibitor), he/she will wait a minimum of 6 weeks prior to the start of the rTMS treatment.

The exclusion criteria are as follows (any of the following): psychiatric conditions/disorders or current neurological or medical disorders, other than Alzheimer disease, that could interfere with cooperative participation (eg, severe agitation and prominent anxiety); diagnosis of intellectual disability; impaired vision or hearing severe enough to impair performance in cognitive tests; exclusive diagnosis of other forms of dementia (including posterior cortical atrophy); primary psychiatric disorders (eg, schizophrenia and bipolar affective disorder) or current and/or unstable neurological, systemic, or medical disorders (eg, liver disease, congestive heart failure, and severe chronic obstructive pulmonary disease [COPD]) that may impair cognition or the ability to complete the required study procedures; use of benzodiazepines and zopiclone during the study and preceding 2 weeks; use of high doses of antipsychotics (based on clinical judgement) that may impair cognition during the study and preceding 2 weeks, or situations where changes in antipsychotic doses can reasonably be anticipated; participation in a clinical trial with any investigational agent within 2 weeks prior to study enrolment; current substance abuse disorder; history of epileptic seizures or epilepsy; contraindication for receiving TMS treatment according to a TMS questionnaire; inability to adequately communicate in English at Manitoba and Australia sites and either English or French at the Montreal site; previous treatment with rTMS within the past 3 months; and any plans to change medication for Alzheimer disease, mood disorders, or pain during the study. Neuropsychiatric symptoms that are considered secondary to Alzheimer disease are not considered in the exclusion criteria, except where they would make it difficult to comply with study requirements, as described above.

Following the initial screening process, we will obtain a magnetic resonance imaging (MRI) scan of the participant’s head. An MRI scan is required by the neuronavigation software in order to position the TMS coil accurately over the target brain region. If a clinical MRI scan already exists, which is suitable for our needs (adequate resolution and coverage to identify and locate internal and external reference points used by the software), we will obtain it from the medical records. If there is no previous clinical MRI scan or the previous MRI scan is not adequate for our research purposes, we will schedule and pay for a research MRI scan to be completed for the participant.

Before performing the MRI scan, we will ask participants if they have any implants, devices, or objects that can be hazardous to them and/or may interfere with the scan. If they express any concerns, we will consult with the MRI clinic and/or ask them to consult with their family doctor. If we still cannot retrieve a valid MRI scan, a reference head model will approximate the participant’s anatomy.

When a scan is performed for the purpose of this study, the following scanning parameters will be used: T1-weighted scan; voxel resolution, 1 mm^3^; matrix, 256×256; and field of view, 25.6 cm (to match the matrix and resolution). The tip of the nose and both ears are required to be included in the scan.

If patients have any medical implants, devices, or objects that could be hazardous to them during the rTMS treatments, we will ask them to consult with their family doctor and provide their doctor’s confirmation via a written document that rTMS can be safely applied for their continuation in the study.

Prior to study participation, all patients and their primary caregivers will be required to sign an informed consent form approved by the ethics board of each site of the study.

### Randomization

Once enrolled in the study, each participant will be assigned to a treatment group (either sham or active, as well as either 2 or 4 weeks of treatment), using stratified block randomization (block size of 3). There will be four distinct stratification blocks using two levels for two factors (age and severity) as follows: age ≥70 years, CDR=1; age ≥70 years, CDR=2; age <70 years, CDR=1; age <70 years, CDR=2.

Group assignment will be determined using an automated algorithm. The only person who will know the group assignment for a given participant is the rTMS administrator at each site who provides the age and CDR data for the algorithm and informs the participant of the duration of treatment. Blinding of the site coordinator will be broken only when necessary to ensure patient safety, that is, in case of a serious adverse event where clinical follow-up is necessary.

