The primary outcome measure will be the change in patient scores from baseline on the ADAS-Cog assessment, as that is the most common standard test used in dementia clinical trials. Alternate forms of the ADAS-Cog word lists will be used at each visit to avoid possible practice effects. The secondary outcome measures will be the change in the scores from baseline of the proximal measures Stroop test [53] and verbal fluency test, as well as the distal measures NPI-Q and ADCS-ADL. We will also assess the tolerability of the rTMS treatment by the TSQM [54], which will be completed by patients and their primary caregivers posttreatment.

At each site, the above assessments will be administered by a study research assistant (RA) blinded to the group assignment of the patients. The RAs involved in administering treatment or assessments will not be involved in any of the statistical data analyses.

**Table 1 table1:** Date adjustments for assessments.

Assessment	Range of possible dates
Baseline	Up to 1 week before the first treatment
Week 3	+/− 1 day of the ideal date
Week 5	+/− 1 week of the ideal date, but after the final treatment
Week 8	+/− 1 week of the ideal date
Week 16	+/− 2 weeks of the ideal date
Week 24	+/− 2 weeks of the ideal date

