#### Analysis of the Results

Baseline characteristics will be assessed between the active and sham treatment groups by descriptive statistics, as well as formal statistical tests. Baseline differences between the two groups, if any, will be adjusted for in the final statistical analyses. All assessment scores will be checked for normality of distribution to determine the choice of either parametric or nonparametric methods. Bartlett statistic will be used to assess the homogeneity of variances, and Levene [56] or Brown-Forsythe [57] tests, which are less sensitive to departures from normality, may also be used. In all instances, a *P* value <.05 will be considered significant.

To test H1 and H2 (the efficacy of rTMS treatment), two-factor (active vs sham) repeated (pre-post treatment) analysis of variance (ANOVA) will be used to investigate the effect of treatment before and after the 4-week block of treatment. The dependent variable will be the change in the ADAS-Cog score (primary outcome measure). Testing H3 will be similar to the tests of H1 and H2, but the two factors will be the two durations of treatment.

For secondary outcome measures, a two-factor ANOVA will also be used in the same way as described above, but a Hochberg test [58] will be applied to correct for multiple comparisons.

The last-observation-carried-forward method will be used in the case of missing data or premature termination.

To test H4 (the durability of rTMS treatment), repeated measure ANOVA will be used among responders (those who show improvement in the ADAS-Cog score of ≥3 points over the course of treatment [3] in both groups) to investigate the duration over which the improvement may last. Post-hoc follow-up methods, such as Dunnett [59] and Tukey [60] tests, will be applied as needed. In addition, a mixed regression model will be developed to predict the response variable at each assessment visit of the active treatment group (both treatment arms separately). The independent variables will be patients’ current age and the severity of Alzheimer disease (as measured by the CDR).

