### Quality Assurance

A designated study coordinator will travel and visit the study sites approximately three times per year to ensure that each site is adhering to the study protocol. They will also ensure that the three sites are consistent in the details of implementing the study protocol, such as RMT measurement and assessment techniques.

Before the study starts, after the RAs are hired, the principal investigator (PI) and co-PIs at each site will have an online meeting to go through the protocol and procedure entirely. All the RAs will be trained and will fully practice their specific tasks before the study starts. If there is any issue of ambiguity raised during this meeting, the PI and co-PIs of the sites may schedule a follow-up meeting to discuss the issue and ensure the group is in agreement on the intended protocol.

The study coordinator’s job is to ensure that the three sites are synchronized in terms of adherence to the protocol. Before the first visit of the site coordinator, the PIs of each site will meet virtually by video conferencing to go over the details of the protocol and how they plan to ensure the staff at each site will be trained to perform the protocol in exactly the same manner at every site. The first visit of the coordinator will be during the first months of the study when the treatment of the first block of patients starts. During each visit, the study coordinator will attend at least one treatment and one assessment to be able to evaluate the procedures and flag any inconsistencies across the sites. In addition, the coordinator is responsible to oversee the overall data management in the main server located in Manitoba, as well as monitor and communicate across the three sites on an ongoing basis to ensure compliance with the protocol at every site.

All outcome assessment data will be uploaded and saved on the PI’s Biomedical Engineering (BME) server in Manitoba, which is a secure server that is being administered by a dedicated computer engineer. A standard routine of anonymization will be in place to assign a code to each patient and ensure the safety and security of patient data.

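### Site is neither a randomisation stratum nor a named term in any model; prespecifying it as a three-level fixed effect is a small, nearly free gain in precision

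*Protocol article*

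**What the plan says.** The Experimental Design section names "three sites contributing to the study (Winnipeg, Montreal, and Melbourne" as the recruiting centres. Under Randomization, participants are allocated "using stratified block randomization (block size of 3"), and the strata are listed in full: "There will be four distinct stratification blocks using two levels for two factors (age and severity"). The inputs to allocation are equally explicit: it is "the rTMS administrator at each site who provides the age and CDR data for the algorithm". Site does not appear.

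Under Analysis of the Results, for H1 and H2 a "two-factor (active vs sham) repeated (pre-post treatment) analysis of variance (ANOVA) will be used", with change in ADAS-Cog as the dependent variable. The mixed regression in the same section uses age and CDR. Two further provisions allow adjustment: one for baseline differences between the groups if there are any, the other for covariates whose imbalance is statistically significant. Neither names site.

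Site is handled operationally. The Outcome Measures section says: "At each site, the above assessments will be administered by a study research assistant (RA) blinded to the group assignment". The Quality Assurance section sends a coordinator to the sites to "ensure that the three sites are consistent in the details of implementing the study protocol, such as RMT measurement and assessment techniques", and sites check one another's scoring. The Recruitment section requires English at two sites and "either English or French at the Montreal site".

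**The concern.** In a three-site trial, site often predicts outcome, and this protocol takes practical steps to keep sites alike. The analysis has no counterpart to those steps. If mean ADAS-Cog change differs between sites, through case mix, rater drift or practice effects, that variation inflates the residual error for H1 and H2. Because the listed strata do not include site, the arms may also be unevenly spread over sites by chance, and the model as written does not correct for it. Adding the randomisation strata to the model would not help, since site is not one of them. What is at stake is the precision of the treatment difference and how it reads if one site happens to carry a surplus of one arm.

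**Working it through.** **Inputs.** From Sample Size Estimation: difference 3 points, SD 4.9, 63 per group, 189 in total, alpha .05 with Bonferroni correction for three groups, power 80%. Assumptions, because the documents give no figure: three equal sites, and H1 comparing the two active arms pooled (126) with sham (63). Differences between sites in mean change are varied from 1 to 4 points.

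**The plan's own figure.** n per group = 2[SD(z_α + z_β)/d]².
- At the stated level, two-sided 0.05/3: 2[4.9(2.394 + 0.842)/3]² = 55.9, so 56.
- At two-sided 0.01: 2[4.9(2.58 + 0.84)/3]² = 62.4, so 63.

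The 63 therefore matches 0.01, not 0.05/3. That is a separate matter, but it affects the power margin below.

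**Chance imbalance, H1.**
- SD of the difference between arms in one site's share: √[(1/3)(2/3)(1/126 + 1/63)] = 0.073.
- If that site's mean change differs by 2 points, the 1-SD shift is 2 × 0.0727 = 0.145 points, and the 2-SD shift is 0.29.
- SE of the H1 estimate without site variation: 4.9√(1/126 + 1/63) = 0.756.
- Added share of variance: (0.145/0.756)² = 3.7%.

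**Residual error, same scenario.**
- Between-site variance: 2² × (1/3)(2/3) = 0.889.
- Relative to 4.9² = 24.01: 0.889/24.01 = 3.7%.
- SE ratio: √1.037 = 1.018.

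The two percentages agree because they are one quantity seen twice. The unadjusted SE already contains the chance imbalance.

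**Power without a site term.** One active arm against sham, 63 each, with sites at −r/2, 0 and +r/2, so the added variance is r²/6:

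| Spread r | Total SD | Power at 0.05/3 | Power at 0.01 |
|---|---|---|---|
| 0 | 4.90 | 85.1% | 80.5% |
| 1 | 4.92 | 84.9% | 80.2% |
| 2 | 4.97 | 84.0% | 79.2% |
| 3 | 5.05 | 82.6% | 77.6% |
| 4 | 5.16 | 80.7% | 75.3% |

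For the pooled H1 comparison (126 against 63) at 0.05/3, power is 94.2% with no site variation and 91.5% at a 4-point spread.

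**Simulation.** 189 participants, three sites of equal expected size, four strata, blocks of 3, one active arm against sham, alpha 0.05/3.
- The 95th percentile of the absolute shift from site imbalance was 0.14, 0.29, 0.41 and 0.57 points for spreads of 1, 2, 3 and 4.
- Mean estimates lay between 2.97 and 3.03 for a true 3.
- Under no effect, rejection rates without a site term were 1.5% (2-point spread) and 1.8% (4-point spread), against a nominal 1.67%.
- At a 4-point spread, power was 79% with neither stratum nor term, and 84% with the site term, whether or not site was also a stratum.
- At spreads of 1 and 2 points, the site term alone made no visible difference to power.

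**The case against.** The strongest reply is that nothing here is an error. Randomisation makes the unadjusted estimate unbiased, its standard error already allows for site variation, and covariate lists are often left to a fuller document. All of that stands, and it rules out several stronger readings.

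- *Bias or false positives.* A reader might infer that imbalance across sites biases H1 or inflates type I error. It does neither, by theory and in the simulation.
- *Two harms.* Residual variance and chance imbalance look like separate problems; the working shows they are the same 3.7%.
- *Raters and language.* One might infer that different assessors and possible French testing distort the comparison. The outcome is change from baseline, and the Outcome Measures section keeps one assessor per participant throughout, so constant offsets cancel. Language can vary within Montreal, so a site term would not isolate it.
- *Stimulation delivery.* Differences in motor-threshold measurement or coil handling would act mainly under active stimulation, because the sham coil attenuates the field. That is treatment-by-site variation, which an additive site term does not model.
- *Quality assurance as an admission.* Training, visits and cross-checking are mitigation, not evidence that sites differ materially.

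It is also unstated whether the algorithm keeps a separate list at each site, which would balance site implicitly. What survives is narrower. The strata and model factors are enumerated without site, and the conditional adjustment rules are tied to observed or significant imbalance. A rule of that kind recovers no precision when arms happen to balance.

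**Conclusion.** The point holds as a minor one. As written, between-site differences in mean change stay in the error term and chance imbalance across sites is not corrected. Under the assumed 2-point difference at one of three equal sites, this costs about 3.7% in variance and under 2% in standard error. A site effect as large as a 4-point spread would exceed the 3-point treatment target itself.

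At the stated 0.05/3 level, analytic power stays above 80% across the range examined. Simulated power dips to 79% only at a 4-point spread. If the operative level were the 0.01 that reproduces 63 per group, a single-arm comparison has no margin, and a 2-point spread takes it from 80.5% to 79.2%. Even that is a loss of about one point.

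These sizes rest on assumed site differences, equal sites and a 2:1 pooled comparison for H1. The documents support no between-site variance, so they do not show that the trial's conclusions are at risk.

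**What to change.** Before unblinding, state that site (three levels) enters the H1 and H2 models as a fixed effect on change, together with the age and CDR strata, for ADAS-Cog and the secondary outcomes, regardless of any baseline imbalance test. If the repeated-measures form on pre and post scores is kept, the term must be site-by-time, because a site main effect there would act on level and not on change. Report the treatment difference by site descriptively, since differences in delivery would show up there. Confirm in the same place whether allocation lists are separate by site.

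The cost is one sentence and two degrees of freedom. Site is identifiable for every participant, and with enrolment under way randomisation need not change. Fixing the term before unblinding matters because adding it later would look data-driven.

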### Treatment Protocol

Patients in both the active and sham treatment groups will undergo daily (5 days/week) rTMS treatment. Each treatment will apply 25 trains of rTMS pulses bilaterally to the DLPFC. Each train will have a duration of 1.5 s, and pulses will be applied at 20 Hz (for a total of 30 pulses per train). The intertrain interval will be 10 seconds. Thus, there will be a total of 1500 pulses delivered to the brain per day (25×30=750 per side), resulting in a total of 30,000 pulses applied over the course of 4 weeks of treatment (20 sessions) or 15,000 pulses for 2 weeks of treatment (10 sessions). Each TMS treatment session will take approximately 10 to 25 minutes. Any missed treatment sessions will be made up on the following day, with a minimum 30-minute break between sessions.

The pulses will be applied at 90% to 100% of the RMT of each participant. The RMT, which will be measured for each hemisphere before the first treatment, is determined by applying single TMS pulses over the primary motor cortex and observing the lowest intensity at which it causes an involuntary twitch of the participant’s contralateral thumb. The specific process involves setting the intensity of the stimulator at 65% to 75% of the maximum intensity and adjusting the coil location over the primary motor cortex until the “hotspot” for activating the involuntary twitch is found. Then, the intensity is lowered in 1% decrements to find the lowest intensity at which an involuntary twitch can be clearly observed in three consecutive pulses. The intensity of treatment will be 90% to 100% of the RMT, unless the participant is having trouble tolerating the treatment, in which case treatment at an intensity of 90% of the RMT will be used for the first session and increased to the full dose of 100% by the end of the first week of treatment.

The location of the DLPFC will be determined using the BrainSight 2 navigation system [52] for TMS. The right and left DPLFCs of each participant will be localized using their own MRI scan, and the coil location and direction will be specified using the BrainSight software at Talairach coordinates (x, y, z) = (–50, 30, 36). The coil will be held at approximately 45 degrees relative to the horizontal axis, but this will be measured approximately rather than specified exactly using the neuronavigation software.

To prevent unblinding, a Magstim sham coil will be used for sham treatments. This coil provides the same sound and tactile sensory experience as the real coil, but it attenuates the strength of the induced electrical field in the brain well below the threshold required to stimulate neurons. In addition, during treatment, only the participant and the research personnel designated to administer the rTMS will be present (no caregiver).

